### Recruitment

Patients enrolled in the intensive phase of anti-TB treatment will be recruited by the research support team of healthcare professionals from each health facility, based on the eligibility and exclusion criteria. The recruitment will be continued until the required sample size is obtained. All the recruitment process details will be recorded on paper forms and kept securely by the facilities until the project is completed.

### Randomization and allocation

Participants will be centrally randomized into one of the two groups using simple randomization in computer-generated algorithm, with an equal allocation ratio (1:1), by members of the research support team, who will not be involved in measuring the outcome (Fig 4).

**Fig 4 pone.0261758.g004:**
[figure not shown]
Flow diagram for Ma-MAS intervention trial.

### Follow up

Both the intervention and control groups’ patients will be followed for an equal period of 2 months. Intervention group participants will receive a total of 60 daily SMS text reminders and 8 phone calls for medication intake and refill visits reminders.

### Blinding

Single-blinding will be applied to avoid bias in outcome measurement, by differentiating the person who measures the outcome from the person who randomizes and provides the intervention. Thus, the person who measures the outcome will be blinded as to which group participants are assigned. Due to the nature of the trial intervention participants will not be blinded to which group they are assigned.

### Implementation

All patients assigned to any group will get the same standard treatment based on the Ethiopia National Tuberculosis Treatment guideline which is rifampicin, isoniazid, pyrazinamide and ethambutol for two months followed by rifampicin and isoniazid for four months [50]. Patients screening, enrolment, consenting and randomization will be undertaken by the research support team, who have health professional backgrounds. An open SMS automation software platform will be used to store, monitor, and send SMS texts. Global system for mobile (GSM) sim card and short code SMS credit will be used to send the SMS texts. SMS text traffic will be managed and monitored in one centralised computer database server by trained IT personnel. The maximum size of an SMS text will not be more than 160 characteristics. A weekly phone calls will be made to the intervention group participants from the health facility by delegated members of the research team. A checklist of questions will be recorded at each time the weekly phone calls are made to the participants (S2 Checklist). Bothe the SMS text and Phone calls intervention will be made using the national official language which is Amharic. For patients who do not answer phone calls, three repetitive attempts will be made at five-minute intervals. All SMS texts and phone calls will be delivered at a similar time in the morning before the actual medication time. The message delivery reports will be continuously monitored to ensure the participants have received the SMS texts as planned. Participants will also be asked whether they are receiving the SMS text every week through phone calls and when they come for their medication refill visit. Participants will be briefed on the duration, frequency, and timing of SMS text and phone calls intervention and advised to turn on their mobile in the morning. Participants will be informed about the intervention and instructed not to tell and/or share the SMS texts or phone calls with other people. If participants lose or change their phone numbers, the new phone number will be replaced immediately after they have informed a support team member. The trial will be audited with participant enrolment, consent, allocation, and during the intervention period.

### Data collection and management

A trained healthcare professional team will collect and supervise the data collection. Data collection will be made after the patient has received the routine non-daily DOT services in a different room from the TB clinic room, to ensure the confidentiality and privacy of the patient’s information. The data will be collected electronically using a smart mobile app through a questionnaire coded using Open Data Kit (ODK). Data will be collected from the primary source through interviews and sample urine collection, and secondary source by a review of the health facility attendance registration book to confirm the patient’s medication refill visit attendance. All interviews will be conducted after the patients finish the non-daily DOT service. Interviews will be conducted in a different room from the TB clinic to be convenient for discussion and privacy.

To ensure the security of the patients’ information, all data will keep in Open Data Kit (ODK) database, principal investigator laptop computer, and backup file with password protectors. All identifiable information will be removed and replaced by code. All hard-copy research documents will be locked in a cabinet.

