**Methods:**

This study is a single-blind parallel-group design individual randomized control trial. A total of 186 participants (93 per group) will be individually randomized into one of the two groups with a 1:1 allocation ratio by a computer-generated algorithm. Group one (intervention) participants will receive daily SMS texts and weekly phone calls concerning their daily medication intake and medication refill clinic visit reminder and group two (control) participants will receive the same routine standard treatment care as the intervention group, but no SMS text and phone calls. All participants will be followed for two months of home-based self-administered medication during the continuation phases of the standard treatment period. Urine test for the presence of isoniazid (INH) drug metabolites in urine will be undertaken at the random point at the fourth and eighth weeks of intervention to measure medication adherence. Medication adherence will also be assessed by self-report measurements using the AIDS Clinical Trial Group adherence (ACTG) and Visual Analogue Scales (VAS) questionnaires, and clinic appointment attendance registration. Multivariable regression model analysis will be employed to assess the effect of the Ma-MAS intervention at a significance level of P-value < 0.05 with a 95% confidence interval.

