The World Health Organization (WHO) recommended Direct Observation of Treatment (DOT) by a trained supervisor; a health worker or a treatment supporter watches the patient take their antibiotics every day to ensure adherence [15]. However, evidence shows that DOT does not necessarily provide a reliable solution to poor TB treatment adherence [16, 17]. In Ethiopia, implementing DOT is also very challenging for patients as it requires patients’ daily visits to the health facility, which has undesired implications in their work, social life and high transportation cost [18, 19]. The current WHO recommendations are to consider DOT implementation with different administration options including conventional DOT, video-observed treatment (VOT), and non-daily DOT [20]. The non-daily DOT has been implemented in Ethiopia, in which during the first two months of the intensive phase of treatment patients take their daily medications with the supervision of the healthcare provider, and from two to six months in the continuation phase of treatment patients take all their medications at home and visit a clinic weekly to refill their medications [11, 19]. However, the non-daily DOT schedule has been interrupted by the COVID-19 pandemic [21].

Digital health interventions through mobile health can create new opportunities for healthcare improvements, especially in situations with limited infrastructure, expertise, and human resources in the healthcare system [22–25]. Digital health interventions that enhance TB medication adherence are seen as a promising option to bring health benefits to the community [26]. The growth in popularity of mobile phones provides opportunities to address adherence challenges related to DOT, as mobile health can facilitate direct communication between healthcare providers and TB patients through SMS and voice calls along with DOT or non-daily DOT [27, 28]. Along with SMS text reminders, phone calls are also suggested to improve a patient’s clinic attendance and treatment outcomes, and can also be used to make the SMS text intervention interactive [29, 30]. In Ethiopia, access to mobile phones is expanding widely: according to the Ethiopia Demography Health Survey (EDHS) 2016, 88% of urban households and 47% of rural households have mobile phone access [31]. This is substantial growth over 5 years when compared to the EDHS 2011, which indicated 65% of urban households and 13% of rural households had mobile phone access [32].

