### Study setting

The study will be conducted at the primary public health facilities of Addis Ababa, Ethiopia. Addis Ababa is the capital city of Ethiopia, and the city has 11 administrative sub-city regions. Based on population projection the estimated total population of Addis Ababa in 2017 was 3,433,999 with 1,624,999 Males and 1,809,000 Females [38]. In Ethiopia, a DOT program has been implemented in two phases, “intensive” and “continuation”. In the intensive phase (daily DOT), a patient takes their medication in front of the healthcare worker every day at a health facility. In the continuation phase (non-daily DOT), a patient is given the responsibility to take the medication at home and come to a health facility weekly for health checking and medication refilling [39].

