### Outcome

The outcome of the trial is the medication adherence of the patient, measured by both direct and indirect methods of measurement. The primary outcome will be measured using an IsoScreen test (GFC Diagnostics Ltd, Bicester, England) for the presence of isoniazid (INH) drug metabolites in urine in accordance with the vendor-supplied user manual. The IsoScreen test result is negative when there is no colour change (i.e. the strip remains yellow) after 5 minutes, and the test result is positive when the colour changes to dark purple, or blue/ green in that time, depending on the concentration of the medication (i.e. if the medication was taken in the last 24 hours or 48 hours respectively) [44, 45]. The IsoScreen test will be done at the fourth and eighth weeks of the intervention. The proportion of adherence measured by the IsoScreen test at the eighth week of the intervention (primary end point) will be used as the primary interest of analysis. The proportion of adherence measured by the IsoScreen test at the fourth week of the intervention will be used as the secondary interest of analysis.

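### As written, the week-8 urine sample follows the weekly refill, so a dose from the new supply could not be told apart from home dosing; the size of the effect is unknown and may be zero

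*Protocol article*

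**What the plan says.** Four statements in the protocol article bear on this point.

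- **Order.** Data collection and management: "Data collection will be made after the patient has received the routine non-daily DOT services in a different room from the TB clinic room". The reason given is confidentiality and privacy.
- **Urine is part of data collection.** Same section: "Data will be collected from the primary source through interviews and sample urine collection". A later sentence repeats the order but names interviews alone: "All interviews will be conducted after the patients finish the non-daily DOT service".
- **Content of the service.** Study setting says that in the continuation phase "a patient is given the responsibility to take the medication at home and come to a health facility weekly for health checking and medication refilling". The Background agrees that "in the continuation phase of treatment patients take all their medications at home and visit a clinic weekly to refill their medications".
- **Test and endpoint.** Outcome reads the colour of a positive strip as showing "if the medication was taken in the last 24 hours or 48 hours respectively". The IsoScreen proportion at week 8 is the primary endpoint; the week-4 proportion is secondary.

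The Methods part of the abstract adds that the urine test "will be undertaken at the random point at the fourth and eighth weeks of intervention to measure medication adherence". The main text does not say how that fits with sampling after the refill service.

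**The concern.** The endpoint is meant to show whether patients take isoniazid at home without supervision. One recent dose is enough for a positive strip. If urine is given after the refill, a patient who arrived with no tablets has just received some and could take one before the sample. The strip would then read adherent for someone whose home dosing had lapsed.

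Such a patient is one the test is meant to identify. Any conversion runs in one direction, from negative to positive. It would lower the observed non-adherence rate in both arms and reduce the absolute difference that the trial is sized to detect. The control arm is planned to hold more negatives, so more would be lost there in absolute terms.

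**Working it through.** **Step 1: the order of events.** Data collection follows the non-daily DOT service; urine is one of the data collected; the service includes the refill. Taken together, urine follows the refill. The abstract's random point concerns when in weeks 4 and 8 the test falls and does not alter the order within a visit. If it means sampling away from refill visits, it conflicts with Data collection and management. Either way the two sections need reconciling.

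**Step 2: who is exposed.** A patient who skipped doses but still holds tablets could take one before arriving, so the refill gives that patient no new opportunity. Only a patient with no tablets left gains one. The share f of otherwise negative patients who are converted is therefore a product:

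f = (share with no tablets left) × (share of these who take a dose between refill and sample) × (share of those doses detectable by the time of sampling)

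The documents give none of the three. If any is zero, f = 0.

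**Step 3: the planning figures.** Sample size gives non-adherence of 25.6% (control) and 10.6% (intervention), a difference of 25.6 − 10.6 = 15.0 points, with 81 per arm before attrition. The usual two-proportion formula with pooled variance returns 81 at one-sided 0.05 and 80% power; at the stated one-sided 0.025 it returns 103. That mismatch is a separate matter and is not evidence for this point. Power is shown below under both settings for that reason.

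**Step 4: effect of a common f.** Assume that f is the same in both arms and that the planning rates apply to IsoScreen. The observed rates become (1 − f) × 25.6% and (1 − f) × 10.6%, and the difference (1 − f) × 15.0 points.

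| f (assumed) | Control | Intervention | Difference | Power, 81 per arm, one-sided 0.05 | Power, 81 per arm, two-sided 0.05 |
|---|---|---|---|---|---|
| 0 | 25.6% | 10.6% | 15.0 points | 80.3% | 70.2% |
| 10% | 23.04% | 9.54% | 13.5 points | 75.6% | 64.5% |
| 20% | 20.48% | 8.48% | 12.0 points | 70.3% | 58.4% |

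Two-sided 0.05 is equivalent here to one-sided 0.025.

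**Step 5: the risk ratio.** [(1 − f) × 10.6] / [(1 − f) × 25.6] = 10.6/25.6 = 0.41 for any f below 1. With a common f the risk ratio of non-adherence does not move; the absolute difference and the power fall.

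**The case against.** The strongest case on the other side is that the stated order does not amount to a biased endpoint.

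- **No dose at the visit is described.** Background and Study setting place continuation-phase dosing at home. This stands as a limit on what can be claimed. It describes intended practice, however, and does not prevent a dose between refill and sample.
- **Detectability is unknown.** Outcome gives a look-back window of 24 or 48 hours, not the time from swallowing to a positive strip, and the interval from refill to sample is not stated. If that interval is too short, f is zero. This stands in full.
- **Few patients are exposed.** As step 2 shows, the refill matters only to those with no tablets left. Clinic attendance, a secondary outcome, already records late refills. This also stands.
- **The planning rates may not transfer.** Sample size takes its rates from earlier studies and does not say that they came from a urine test. This stands, and the table is conditional on it.
- **The order may not have been written with urine in mind.** The sentence gives privacy as its reason, and the restatement names interviews only. It is therefore too firm to say that urine can only be taken after the refill. Even so, the general sentence exempts nothing, and the plain reading puts urine second.
- **A journal article condenses.** The absence of a time-of-last-dose field is not a fault in itself, since forms are commonly kept elsewhere. The point rests on the order that the article does state.

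A reader might go further and infer that the primary endpoint is biased by a known amount, or that the intervention could appear to work when it does not. The documents support neither. They give no value for f, and a common f dilutes the difference without creating a benefit. Participants are unblinded, so f could differ between arms, but nothing in the documents shows that it does.

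**Conclusion.** The point holds in a limited form. As written, the urine sample for the primary endpoint comes after the refill, which leaves open a plausible route by which a patient who had run out could be classed as adherent. Whether the route is ever used, and whether such a dose would show in time, cannot be settled from the documents, so the size is unknown and may be zero. On the assumptions of a common f and planning rates that carry over to IsoScreen, the 15-point difference would shrink to 13.5 points at f = 10% and 12.0 at f = 20%, with the risk ratio unchanged. The values of f are illustrations, not estimates. The case for acting is that the change is cheap and protects the primary endpoint; no loss of effect has been demonstrated.

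**What to change.** - Collect the week-4 and week-8 urine samples on arrival, before the refill is dispensed. Keep the interviews after the service as planned; the privacy reason for a separate room is still met.
- Record the time of the sample and the reported time of the last dose.
- Reconcile Data collection and management with the random-point timing in the abstract, and state when urine is taken relative to dispensing.

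An analysis that leaves out samples given after a dose at the facility should not be added. With urine taken on arrival there should be almost none, and excluding them would condition on reported behaviour after randomisation in a trial with unblinded participants, contrary to the intention-to-treat analysis of all randomised participants under Statistical analysis.

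The cost is a change in visit order and two recorded times, with no extra visit, staff or test. The outcome assessor must meet the patient both before and after the service. The change does not deal with a dose taken from leftover tablets before arrival.

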### Statistical analysis

The electronically collected data will be exported to STATA and cleaned using STATA coding programing language. Descriptive statistics of mean, standard deviation, median, and range will be used for continuous variables and frequency and percentage for categorical variables.

Intention to treat (ITT) analysis will be performed for all randomized participants according to their group. A chi-square test for binary outcomes and Student’s t-test for continuous outcomes will be used as appropriate. For primary and secondary interest of analysis, multivariable regression model analysis will be employed to adjust confounding factors in the statistical effect. A P-value of less than 0.05 will be used as a cut-off point to show a statistically significant association between Ma-MAS intervention and medication adherence with a 95% confidence interval.

### Ethical considerations

The research proposal has been approved by the Southern Adelaide Clinical Health Research Ethics committee (SAC HREC) on April 8, 2020, with Office for Research (OFR) number: 23.20. The proposal has also be approved by the Addis Ababa Health Bureau ethics committee on August 21, 2020, with reference number A/A/H/930/227 and an official permission letter is provided from Addis Ababa Health Bureau to respective sub-city and health facilities. Each participant will complete a written informed consent form after being informed about the research objectives, procedures, anticipated risks, and benefits of the research. The research team will be confirming or renegotiating consent with participants for additional data. The principal investigator will be ensuring participants are confirming their consent to participation. Participants have the right to withdraw from the study at any time when they feel uncomfortable or unable to continue in the study, and they will be informed of its limitations or consequences on the research during consent requests. Any change in the study protocol and participant informed consent will be submitted to SAC HREC before implementing the change. This trial has no forms of inducement, coercion and the study does not bring any risks that incur compensation in cash or kind.

### Publication and dissemination of the result

The trial findings will be reported based on the Consolidated Standard of Reporting Trials (CONSORT) guidelines. The research outcomes will be published in an international peer-reviewed open access journal. The research outcomes will also be presented at selected national and international conferences. The principal investigator is responsible for disseminating the finding to Health facilities, Addis Ababa Health Bureau, Federal Ministry of Health (FMOH), Flinders University, national and international conferences. The participants will be asked whether they wish to get a summary of the research work, and if so in what form, and will be informed about how they can access the research results. In the case of a formal request for further research purposes, non-identifiable secondary data may be granted to others. A participant’s identifiable information will be removed and replaced by code to protect the anonymity of the participants. Identifiable data and/or information will not be accessed or granted to others.

The trial is registered in the Pan-Africa Clinical Trials Registry with trial number PACTR202002831201865.

## Discussion

An adherence intervention needs to address the underlying factors that cause medication non-adherence [26]. Medical Research Council (MRC) guidelines recommend using appropriate theory and evidence when developing an intervention [40]. However, most adherence interventions are developed without a strong theoretical base, which might be one of the reasons they have not been effective [51]. In this randomized controlled trial, the Mobile-assisted Medication Adherence Support (Ma-MAS) intervention will be developed systematically using the MRC conceptual framework with an appropriate selection of behavioural theory.

Some evidence has shown that interactive SMS texts may have a better impact than using simple SMS text reminders in improving medication adherence [52, 53] although there is also inconsistent evidence found in some two-way [30, 54] and one-way SMS text studies among TB patients [55, 56]. This trial was designed to test an intervention with a combination of daily SMS text and weekly phone calls for medication intake and medication refill visit reminders during the continuation phase of treatment for a two months period, which was not studied previously.

When testing an intervention with randomized trials, correctly measuring outcomes in the same way for both the intervention and control groups is crucial. The accuracy of adherence measurement is very important to assess the true effect of an adherence intervention. Here the adherence outcome will be measured through the combination of a direct method (IsoScreen test) and several indirect methods (VAS, ACTG, and clinic attendance registration) of measurement. This will help to avoid bias in outcome measurement. Therefore, this research would provide evidence to help healthcare managers and policymakers to develop strategies that improve Tuberculosis medication adherence and treatment outcomes in general.
